# Utilization and Feasibility of a Wearable Device in Patients With Sedative Effects of Drugs: Protocol for a Prospective Observational Study for the Advanced Respiratory Monitoring Events in Drug Toxicity (ARM-ED) Study

**DOI:** 10.2196/66961

**Published:** 2026-03-19

**Keywords:** wearable device, respiratory biosensor, opioid-induced respiratory depression, illicit drug toxicity, drug toxicity, benzodiazepine toxicity, emergency department

## Abstract

**Background:**

Drug-related deaths worldwide are most commonly attributed to opioids. Opioids and other sedative drugs can cause respiratory depression and airway compromise, leading to hypoxia and death. Device technology and artificial intelligence used to detect drug overdose has the potential to improve outcomes. PneumoWave Ltd has developed a small chest-worn respiratory monitoring device to detect concerning breathing patterns and alert an emergency response.

**Objective:**

The aim of this study is to investigate the feasibility of using the PneumoWave device in hospital patients at risk of respiratory depression.

**Methods:**

This 18-month prospective observational study was performed at the Queen Elizabeth University Hospital, Glasgow. The study investigates the use of the device on 3 groups of patients at risk of respiratory depression due to drugs. This includes patients attending the emergency department (ED) due to sedative drug overdose, patients receiving procedural sedation and analgesia in the ED, and patients receiving general anesthesia in theaters. Consenting participants will have the PneumoWave sensor paired with end-tidal CO_2_ monitoring and regular recordings of vital signs. Usability will be tested by administering a questionnaire to the patient, the clinician, and the nurse. The primary end point is to determine the feasibility of gathering respiratory data from a wearable respiratory monitoring device in the ED. Statistical analysis includes comparison of biosensor data against reference physiology time course data.

**Results:**

Trial recruitment was completed on December 8, 2023. Twenty-five patients were enrolled in group 1 (acute toxicity); 39 patients in group 2 (procedural sedation), including 1 patient who was subsequently withdrawn; and 14 patients in group 3 (acute toxicity), with 2 patients withdrawn. Publication of the study results is anticipated by December 2025.

**Conclusions:**

This study will explore the feasibility of the PneumoWave device in a variety of clinical contexts in which risk of pharmacologically induced respiratory depression is present. This will provide valuable insight into the use of device technology in individuals at risk of illicit drug–related harm within the relative safety of a hospital setting. A limitation of the study procedure is exclusion of patients with intoxication after sedative drug overdose who lack the capacity to provide informed consent. This study has been designed to acquire feasibility data to demonstrate the potential for continuous respiratory monitoring to improve outcomes for patients who are at risk of drug-induced respiratory depression, inform product development, and inform the design of future pivotal clinical investigations.

## Introduction

### Background

Over a quarter of a billion people worldwide used illicit drugs at least once during the year 2021, 60 million of which used opioids. Overdose is a significant cause of preventable morbidity and mortality globally, with approximately 128,000 deaths directly due to drug use in 2019 [1]. Within Europe, Scotland reports the highest drug-related death rate at 19.8 per 100,000 population. This study is sited in a tertiary urban hospital in Glasgow, Scotland. National Health Service (NHS) Greater Glasgow and Clyde Health Board has the highest drug-related death rate in Scotland (34 per 100,000 in 2022), and hence, this research is at the epicenter of the drug death crisis [2].

Opioids are the drug group most commonly attributed to drug-related death in the world [3]. In 2021, opioids were implicated in 75% and 74% of drug-related deaths in the United States and Europe, respectively [4,5]. Similarly, in Scotland, postmortem toxicology reports found that the most commonly implicated drugs were opioids (n=1051, 82.5%) and benzodiazepines (n=1051, 57.2%) [2].

Opioids are μ-receptor agonists, and their overdose can lead to reduced consciousness, irregular or slow breathing patterns, and potentially life-threatening or fatal respiratory depression. Death following the use of opioids is due to loss of respiratory reflexes, apnea, and respiratory failure [6,7]. There is an increased risk of death in opiate-naïve patients when opioids are combined with other central nervous system (CNS) depressant drugs such as alcohol, benzodiazepines, and other co-prescribed medications such as gabapentinoids [8,9]. Overdose of benzodiazepines, like opioids, can lead to reduced consciousness and loss of airway reflexes, leading to potential death. This is the case especially when taken in the context of user naivety, high doses used, potent preparations, or co-ingestion [10,11].

Access to emergency services and the use of the opioid antagonist, naloxone, given by any individual can reduce the risk following drug overdose [12]. A user who experiences an overdose must, however, be able to access help and therefore is at higher risk of death when using drugs alone [13].

The use of technology may help provide a solution to reduce the risk of fatal overdose in drug users. There have been several studies investigating the use of device technology in this setting, and these devices may be attached to or positioned somewhere away from the individual. Mobile phone apps are available for prevention and detection of harm. These often rely on the user (who may be unconscious) being able to alert help via the device [14]. A mobile app described by Nandakumar et al [15] found that a mobile phone which was adapted to use sonar to detect respiratory effort and apnea reported higher performance in the detection of postopioid self-administration central apneic events (10 s or longer). However, the device was required to be held by a second person at a 90° angle and at a distance of just 1 m from the individual for its successful use. Other near-patient devices include in-room movement sensors and help buttons; the latter again require the user to be capable of pressing the button [16,17].

Several wearable sensors in development have been described, including those that deploy naloxone [18-20]. The described devices have major barriers to their potential use. Mesa et al [19] describe a sensor that requires implantation of a drug-delivery system, which would likely not be acceptable to many individuals, with a potential increased risk of infection. Chan et al [20] describe a bulky device, which may reduce compliance of use, and they found it was unreliable in deploying the naloxone. Roth et al [21] describe a commercially available biosensor to detect movement. They showed success in collecting accelerometer data; however, they detected no respiratory depression despite 385 drug administrations recorded (>90% involved fentanyl), 27 of which the user described themselves as having “too much”.

There are some potential barriers to the use of a device such as battery life, effective functioning, size, weight, and aesthetics [22,23]. Despite this, potential users of devices are likely to be accepting the device if they understand its ability to reduce harm [24]. As described, the near-patient device described by Nandakumar et al was limited by its requirement to be perpendicular and within 1 m proximity to the patient to achieve stated results [15]. There is clearly a need for innovative technology that can detect individuals at risk of overdose, enabling help to reach them, while also being acceptable to wear.

### Wearable Technology

PneumoWave Ltd has developed a small, wearable biosensor that incorporates a microelectromechanical system inertial motion unit capable of continuously monitoring central body motion over time [25]. This physical monitor is linked wirelessly (Bluetooth) to central monitoring systems via either a data gateway that plugs into a nearby electrical socket or a smartphone. The company’s technology is separated into two product lines: DC (data collection) and the Alert (event recognition).

PneumoWave DC is a UKCA (UK Conformity Assessed) Class 1 medical device with the following intended use: PneumoWave DC is a monitoring device intended to capture and store chest motion data continuously for retrospective analysis by a health care professional to document physical movement associated with applications in physiological monitoring. The device is not intended for diagnosis of respiratory conditions. It is indicated for patients deemed to be suitable for chest motion monitoring in health care facilities by a physician (Figure 1).

**Figure 1. F1:**
[figure not shown]
PneumoWave data collection system. A clinical data collection and analysis platform showing the biosensor, mobile app, or hub (right image), and clinician web portal with visualization of motion data. This system is designed for researchers and clinicians, with a focus on comprehensive data collection and retrospective analysis.

Prototype biosensor units (identical mounting methods and similar dimensions) were subject to two previous studies resulting in 16,476 hours of wear in 138 participants, indicating a high tolerance for the design (NCT04668313 and ISRCTN12060022). The DCM system collects raw X, Y, and Z axis accelerometer movement data with no data processing applied, which transmits via the App or Hub to a cloud environment. By accessing the cloud dashboard, users are able to view and download the accelerometer data.

The ALERT system for real-time collection of data plus processing is in development to enable detection and the potential of immediate intervention through algorithms currently under development and is a key driver for this study (see Figure 2).

**Figure 2. F2:**
[figure not shown]
PneumoWave ALERT platform technology overview. The biosensor will detect concerning breathing patterns and will send an alert for urgent help for the individual following overdose.

This research investigates the feasibility of the use of the PneumoWave Ltd wearable biosensor in individuals at risk of drug-induced respiratory depression. The safety of a hospital setting has been utilized to understand the feasibility of use. Risk of respiratory depression occurs in a variety of situations within hospitals. As described, an overdose of opioids or other sedating/respiratory depressant drugs often requires medical care and attending the emergency department (ED) for treatment [26]. This group of patients is included in this trial and provides a pragmatic indication of feasibility of use in patients at risk of respiratory depression. Opioids and sedatives are also administered in hospital for medical purposes in a setting where the patient will need respiratory monitoring. One such example is procedural sedation and analgesia (PSA). This is a technique in which sedation is given with an aim to allow a painful procedure to be performed but not deep enough to cause apnea, though there is a risk, and this occasionally does occur [27]. A further example is that of induction for a general anesthetic (GA) where apnea is either certain (with muscle relaxant) or likely (during GA induction). These two groups of patients will also be studied to understand the use of the device in settings of increased risk or definite apnea due to drug administration. End-tidal CO_2_ (ETCO_2_) is used in hospitals in these settings to monitor respiratory rate by capnography and as such is the gold standard comparator in this study [28].

### Study Hypothesis

The PneumoWave device will be well tolerated by patients and will successfully capture respiratory effort and patient movement accelerometer data.

### Objectives

The primary objective of this study was to assess the feasibility of collecting respiratory waveform data using the PneumoWave device in ED patients from groups 1‐3 (see Study Population).

Secondary objectives of the study were as follows: (1) Collate respiratory data from the PneumoWave device and compare to ETCO_2_ in patients from all 3 groups. Respiratory data will observe normal respiratory effort, reduced respiratory effort due to sedating drugs or anesthetic agents, and response to treatments and interventions required in patients with reduced respiratory effort. (2) Collate waveform and motion artifact data from the PneumoWave device in patients from all 3 groups to observe the relationship with the individual’s conscious level. (3) Assess the usability of PneumoWave in the opinion of the clinician, nurse, and patient. (4) Understand the feasibility of gathering respiratory data from a wearable respiratory monitoring device in the ED.

## Methods

### Study Design

This is a single-center observational cohort study conducted using passive non-invasive data collection.

### Setting

This study was undertaken at the Queen Elizabeth University Hospital, Glasgow, United Kingdom, over an 18-month period from June 9, 2022, to December 8, 2023.

### Study Population

The overall study population consists of patients at risk of respiratory depression due to exposure to sedating drugs. The study observes three distinct patient groups:

Group 1 (acute toxicity group): Patients who present to the ED with actual or potential CNS or respiratory depression secondary to toxicological causeGroup 2 (PSA group): Patients who undergo PSA with respiratory and CNS depressant drugs in the EDGroup 3 (GA group): Patients who undergo GA in the anesthetic room in theater

### Inclusion Criteria

The inclusion criteria are presented in Table 1.

**Table 1. T1:** List of inclusion criteria for the Advanced Respiratory Monitoring in the Emergency Department (ARM-ED) study.

Group	Inclusion criteria
All groups	Age >16 years; able and willing (in the investigators’ opinion) to comply with all study requirements; able to speak and read English
Group 1 (acute toxicity)	Willing and able to give informed consent (or via Welfare Attorney, Guardian, or Nearest Relative); presenting to ED^a^ due to presumed overdose of a drug with potential for respiratory depression (intentional, accidental, recreational, or therapeutic excess); having at least one of the following: Glasgow Coma Score (GCS) <15, respiratory depression, or risk of deterioration in GCS or respiration
Group 2 (PSA^b^)	Willing and able to give informed consent; undergoing procedural sedation and anesthesia in ED
Group 3 (GA^c^)	Willing and able to give informed consent; undergoing elective general anesthetic of any type in the anesthetic room

a ED: emergency department.

b PSA: procedural sedation and analgesia.

c GA: general anesthetic.

### Exclusion Criteria

The exclusion criteria are presented in Textbox 1.

Textbox 1.List of exclusion criteria for the Advanced Respiratory Monitoring in the Emergency Department (ARM-ED) study.Unable to provide consent and no next of kin to provide consent on participant’s behalfImpaired consciousness or respiratory suppression most likely due to cause other than acute drug useCondition primarily related to alcohol use and no evidence of acute drug useCondition due to withdrawal of drugs or alcoholTreating clinician deems patient inappropriate to be included in the studyPregnant femalePatient has implantable device (eg, pacemaker)

### Withdrawal of Participants

Participants will be able to withdraw from the study at any time, without impact on their clinical management.

### Sample Size and Rationale

This is a feasibility study to generate data for future prospective interventional studies; therefore, no formal sample size will be generated. The research group planned a target of 50 patients recruited to both groups 1 and 2 as the number of minutes of data capture would successfully answer the primary outcome question of feasibility. Group 3 was included following trial commencement. Following evidence of the volume and type of data being produced from groups 1 and 2, a target of 12 was used based on the understanding of the number of minutes of data gathered. We aim to recruit a total of 112 patients to the study, which will provide adequate data to establish feasibility of use for larger studies. The sample size breakdown is as follows: group 1: 50 patients; group 2: 50 patients; and group 3: 12 patients.

### Primary End Points

The primary end point is understanding the feasibility of gathering respiratory data from a wearable respiratory monitoring device in the ED.

### Secondary End Points

The secondary end points are as follows:

Add to existing respiratory data to inform machine learning and improve sensitivity and specificity of PneumoWave deviceUnderstand the usability of the device within acute care settingUnderstand the feasibility of gathering respiratory data from a wearable respiratory monitoring device in patients undergoing GA

### Outcome Measures

The primary outcome measures will measure the length of time the device is in situ on the patient, the number of times the device is removed by the patient or others, and the ability of the device to collect data while in situ. The secondary outcome measures will observe waveform data from the PneumoWave device and compare those with normal care vital signs and continuous monitoring vital signs extracted from patient monitors. PneumoWave respiratory wave patterns and motion artifact will be compared to clinical events, including normal respiratory patterns, clinical deterioration, and interventions in ED or in anesthetic room in theater, and Glasgow Coma Score.

Stakeholders will be interviewed regarding the usability of the device. These stakeholders are the clinician and nurse caring for the participating patient in question, and the patient themselves, if able to.

Outcome measures and their associated data sources and data capture are shown in Table 2.

**Table 2. T2:** Outcome measures and associated data source and data to be collected.

Outcome measure	Data source	Data to be collected
Primary outcome measures		
Length of time the device is in situ on patient	CASTOR EDC [29]	The total time device present on chest as documented by researcher (seconds)
The number of times the device is removed by the patient or others	CASTOR EDC	Absolute number of times the device was removed
The ability of the device to collect data while in situ	PneumoWave sensor	Total amount data recorded (seconds) as the proportion of time the device was on chest (seconds)
Secondary outcome measures		
PneumoWave device waveform data comparison to clinical events	PneumoWave device and CASTOR EDC	Visual representation of PneumoWave data and comparison to the following: ETCO_2_^a^ waveforms Documented respiratory rate Interventions GCS^b^
Usability of device	CASTOR EDC	Data from results of interview reported in Likert scale from 1 to 5.

a ETCO_2_: end-tidal carbon dioxide.

b GCS: Glasgow Coma Score.

### Study Procedures

#### Potential Participant Identification

##### Group 1 (Acute Toxicity) and Group 2 (PSA) Patient Identification:

Patients from group 1 and group 2 will be recruited concurrently and opportunistically. Patients will be recruited during the research team by the researcher who will observe ED attendances remotely via electronic health records and identify potential participants who are either intoxicated (group 1) or may undergo procedural sedation (group 2). They will assess the patient for eligibility. ED staff will be given information on study recruitment and alert the research team to assess eligibility for inclusion.

##### Group 3 (GA) Patient Identification

Patients will be recruited during specified elective theater lists undergoing a GA. Patients will be approached by the anesthetist for willingness to participate, with the researcher assessing for eligibility, providing them with the patient information sheet, and gaining consent from the patient.

### Consent

Written consent will be gained from the patient or Welfare Attorney/Welfare Guardian/Nearest Relative for group 1 and from the patient only for group 2 and group 3.

### Source Data Collection and Patient Observation

Source data will be collated from multiple sources, including study participant interviews; usual care electronic health records; anesthetic charts; medical, ambulance, and nursing notes; drug charts; and observation charts. Continuous vital sign data will be downloaded from the standard ED or anesthetic monitors or study monitors, PneumoWave sensor data, and manual respiratory rate for study periods using ETCO_2_ monitor.

During the study episode, data will be collected from the above sources for a period of time specific to each group. Data are all gathered by the researcher. Group 1 patients will be observed by the research team member for 1 hour or from commencement of data collection until they are discharged or moved from the ED, whichever is shorter. Group 2 participants will be observed for the duration of their procedural sedation, length of which may vary, and recovery period for up to 15 minutes. Data are gathered from group 3 participants prior to their GA while in the theater’s anesthetic room, during induction of anesthesia and until the patient is moved to the theater.

Usability is investigated by interviewing stakeholders (patient, nurse, and clinician) following each respective research study episode. It is expected that due to the nature of the study, it may not be possible to gather these data for all patients recruited due to reduced conscious level. Responses to domains were on a scale of 1 (least positive) to 5 (most positive). The domains that were investigated were perceptions on device comfort, device intrusiveness, device safety, delay to treatment, acceptability of device in normal practice.

### Review of Notes at 28 Days

The participant has a follow-up review of clinical status at a single time point of 28 days postrecruitment via electronic case records. This will identify any adverse outcome relating to their ED attendance or anesthetic, for example, need for critical care, disability, morbidity, or mortality as well as identify any relevant usual care drug screens performed at the time of assessment.

### Waveform Analysis and Predictive Modeling Algorithms

Data from PneumoWave are analyzed in parallel with deidentified clinical and vital sign observational data to build artificial intelligence–driven predictive modeling algorithms.

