#### Secondary Outcome Measure Analysis

The secondary outcome measures study the data that is captured by the PneumoWave device. In order to analyze this, the device data will be visually reviewed alongside the usual care vital signs and continuous monitoring signs. Respiratory rate calculated from the PneumoWave monitor will be compared to respiratory rate counted by a medical professional from the ETCO_2_ monitor. Accuracy will be analyzed through sensitivity and specificity tests using ETCO_2_ measurements as the gold standard.

Data points in which there has been a change in respiratory pattern, clinical deterioration, clinical intervention, and Glasgow Coma Score will be visually reviewed through time stamp looking at both usual care vital signs and PneumoWave study waveform data. Results will be presented both through written description and visually to highlight waveform changes if applicable.

Analysis of clinician, nurse, and patient opinions on the use of the device will be recorded as median and ranges.

Feasibility was defined as the device remaining attached to the chest with two or fewer removals during the monitoring period and achieving data capture for more than 75% of the total wear time.

The statistical analysis will be performed using MiniTab.

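### One cohort serves both to build the algorithms and to report sensitivity and specificity; unless the software that is scored is independent of these participants, its accuracy figures would be optimistic

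*Protocol article*

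**What the plan says.** Five parts of the protocol article bear on this point.

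- **Wearable Technology** (text after Figure 1): the data collection system stores raw three-axis accelerometer data without processing. The separate ALERT system is to detect events through "algorithms currently under development and is a key driver for this study".
- **Waveform Analysis and Predictive Modeling Algorithms**: "Data from PneumoWave are analyzed in parallel with deidentified clinical and vital sign observational data to build" AI-driven predictive algorithms.
- **Secondary End Points**: the first is "Add to existing respiratory data to inform machine learning and improve sensitivity and specificity of PneumoWave".
- **Secondary Outcome Measure Analysis**: "Respiratory rate calculated from the PneumoWave monitor will be compared to respiratory rate counted by a medical professional from the ETCO_2_ monitor". The next sentence reads "Accuracy will be analyzed through sensitivity and specificity tests using ETCO_2_ measurements as the gold standard".
- **Objectives**: the first secondary objective is to "Collate respiratory data from the PneumoWave device and compare to ETCO_2_ in patients from all 3 groups", so the comparison with capnography covers the whole cohort.

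Strengths and Limitations adds that the study is not powered for diagnostic accuracy and confines its conclusions to feasibility, tolerability and data acquisition.

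**The concern.** An algorithm scored on the participants it was tuned on partly reproduces their noise, so its apparent sensitivity and specificity exceed what new patients would show. The article sets up the conditions for this. The same participants, with the same capnography, are listed as development material and as the accuracy sample. The same two metrics appear once as something the data will improve and once as something the data will measure. The device itself calculates no rate, so the rate that is scored must come from later software, and the article names no version of it.

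At stake is the credibility of a planned secondary result. Expected Principal Findings anticipates waveform data on a par with capnography and an understanding of how accurately the device measures respiratory rate, so readers will look at these figures.

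**Working it through.** **1. Cohort size.** Sample Size and Rationale: 50 + 50 + 12 = 112, which reproduces the stated target. Results: 25 + 39 + 14 = 78 enrolled, and 78 − 1 − 2 = 75 after withdrawals. The document states no accuracy figure, event count or number of candidate features, so no bias can be computed from it directly. What follows is illustration under stated assumptions.

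**2. Real-signal scenario.** Assumptions not in the document: each participant is one observation, 30% have the event, and one feature separates the groups by 1.5 SD while any others are noise. A linear discriminant rule is fitted to n participants (flag an event if w′x > c, with w = S⁻¹(m₁ − m₀) and c = w′(m₁ + m₀)/2). It is scored on those same participants (apparent) and on 2,000 new ones, over 800 runs. Optimism = apparent − new.

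| n | Features | Apparent Se / Sp | New Se / Sp | Optimism Se / Sp |
|---|---|---|---|---|
| 75 | 1 | 0.778 / 0.774 | 0.771 / 0.772 | +0.007 / +0.002 |
| 75 | 5 | 0.797 / 0.796 | 0.742 / 0.764 | +0.056 / +0.031 |
| 75 | 10 | 0.819 / 0.817 | 0.712 / 0.753 | +0.106 / +0.064 |
| 75 | 20 | 0.861 / 0.861 | 0.655 / 0.733 | +0.206 / +0.128 |
| 112 | 10 | 0.803 / 0.800 | 0.730 / 0.760 | +0.073 / +0.040 |

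Differences were taken before rounding, so some differ in the last digit from the columns shown.

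**3. Rule fixed beforehand.** With one feature and a cut fixed at 1.5/2 = 0.75, true sensitivity and specificity are both Φ(0.75) = 0.773. Scored on samples of 75, the means are 0.774 and 0.772, so the optimism is about 0.

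**4. Upper-end illustration.** Suppose all features are noise, 6 or 12 of 75 participants have events, and the best feature with its best cut is chosen. The mean apparent Youden index (Se + Sp − 1; true value 0; 2,000 runs) is then:

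- 6 events: 0.41 with 5 features, 0.52 with 20
- 12 events: 0.31 with 5 features, 0.40 with 20

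On the same scale, the real-signal optimism at n = 75 is 0.007 + 0.002 = 0.009 with one feature, 0.056 + 0.031 = 0.087 with five, and 0.206 + 0.128 = 0.334 with 20.

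**5. Why cross-validation rather than a hold-out.** Taking an observed proportion of about 0.90 and one observation per participant, the exact 95% interval is 0.82 to 0.96 for 68/75 but 0.72 to 0.99 for a held-out 21/23. Cross-validation by participant scores everyone without giving up that precision.

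**The case against.** The strongest reply is that two different things are being joined. The accuracy analysis names a respiratory rate set against a clinician's count; the modelling section concerns AI-driven predictive algorithms; and the algorithms described as in development belong to ALERT, not to the data collection system. No section says that the predictive models generate the rate. Raw output shows only that some method is needed, not that it was tuned here. This stands, and it makes the point conditional.

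Second, the study data are added to existing data, so any training need not rest on these 75 participants alone. This also stands: the simulations train on the study cohort only and could overstate the effect.

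Third, the article condenses protocol version 2.0, and algorithm locking or internal validation may be set out there or in an analysis plan. That is fair, and silence on those details is not in itself an error. What remains is that the article states both uses of one cohort without saying how the scored software relates to the development work.

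Fourth, conclusions are already limited to feasibility. That lowers the severity but does not dispose of the point: low power concerns imprecision, whereas this is bias, and the figures are still planned.

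A reader might infer that the accuracy figures will certainly be inflated, or that the inflation will pass into pivotal studies. The documents support neither. The Abstract says that feasibility data will inform pivotal design, and Future Directions leaves diagnostic accuracy to later trials; neither names the sensitivity and specificity estimates as inputs.

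**Conclusion.** The point holds conditionally. One cohort is used both for algorithm development and for reporting sensitivity and specificity, and nothing in the article establishes that the scored software is independent of it. If that software was built or tuned on these participants and scored without participant-level validation, the estimates would be optimistic; if it was fixed beforehand, they would not be, on this account.

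The size is unknown. With 75 participants and an assumed real signal, the optimism ranges from under 0.01 with one feature to about 0.21 in sensitivity and 0.13 in specificity with 20. The pure-noise Youden values of 0.31 to 0.52 mark the upper end and are not a forecast, since a chest-motion sensor with no true relation to breathing is implausible. Event prevalence, signal strength and feature counts are all assumptions. Severity is minor to moderate: the outcome is secondary and its conclusions are already restricted.

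**What to change.** Add to Secondary Outcome Measure Analysis:

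- Name the method and version that calculates respiratory rate from the accelerometer data, and report sensitivity and specificity for a version frozen and documented before study capnography is merged.
- If study data were used for tuning, report only accuracy from leave-one-participant-out or participant-level k-fold cross-validation, with every tuning step (feature choice, thresholds, filters) inside the loop. Split by participant and not by epoch, because readings from one person resemble each other.
- Label such figures internal development performance and keep them within the limit on conclusions given in Strengths and Limitations.

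Results reports that analysis is in progress, so the first route may no longer be open; the second still is. If the full protocol or analysis plan already fixes this, a one-sentence statement is enough. The cost is wording and computing time, with no new participants. The downside is that the reported accuracy may be lower.
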